During the first week following each study injection, participants will be asked to record local and systemic signs and symptoms using preprinted Participant Diary, a thermometer, and a a local reaction measurement device. In addition to solicited signs, participants will be asked to report any other adverse events. Concomitant medications will also be recorded. Members of the investigator’s clinical team will have contact with participants via phone (C1) on Day 3 (+2) after study injection to check that participants are correctly completing the Participant Diary and to check on the participants’ well-being (occurrence of solicited and unsolicited adverse events).

Participants will return to the study site seven days after study injection, visit S1 on V1+7 (+3) days. At that time, the Principal Investigator or designee will review the Participant’s Diary, confirm the information included and transcribe all solicited and other adverse events onto source document and the case report forms. Blood will be collected for selected biochemical and hematological blood tests. Results of the laboratory tests must be reviewed by the study physician. The study physician will determine the severity grade of laboratory results using the Toxicity Table for Grading Severity of AEs (see section 9). If the result is Grade 2 or higher and clinically significant, the study physician will request repeat laboratory tests. Laboratory results that are Grade 2 or higher and considered to be clinically significant will be followed by the study physician until resolution or stabilization. “Clinically significant” means that the result warrants further medical investigation or treatment because it may have impact on a person’s health status.

Participants will then return to the study clinic 4 weeks after administration of the first study injection (Day 28 + 7). Interim medical histories and concomitant medications will again be reviewed with the participant and blood specimens will be collected for immunogenicity analyses. At visit V2, Day 28 (+7), participants will receive a second study injection (women will have a urine pregnancy test beforehand). If a women is found to be pregnant she will not receive the second study injection and counseling will be provided to them. Blood specimens will be collected for immunological testing prior to administration of study injection. Participants will be carefully monitored for adverse reactions for 30 minutes after study injection.

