During the next 7 days following study injection, participants will be asked to record local and systemic signs and symptoms using a Participant Diary, a thermometer, and a local reaction measurement device. Concomitant medications will also be recorded. In addition to solicited signs, participants will be asked to report any other adverse events. Members of the investigator’s clinical team will have contact with participants via phone (C2) 3 days (+2) after study injection to check that participants are correctly completing the Participant Diary and to check on the participants’ well-being.

On the S2 visit, participants will return to the study site seven days after the second study injection, V2+7 (+3) days. At that time, the Principal Investigator or designee will review the Participant’s Diary, confirm the information included and transcribe all solicited and other adverse events onto the case report forms. Blood will be collected for selected biochemical and hematological blood tests as well as immunogenicity testing. Results of the safety laboratory tests will be reviewed by the study physician. The study physician will determine the severity grade of laboratory results using the Toxicity Table for Grading Severity of AEs (see section 9). If the result is Grade 2 or higher and clinically significant, the study physician will request repeat laboratory tests. Laboratory results that are Grade 2 or higher and considered to be clinically significant will be followed by the study physician until resolution or stabilization. “Clinically significant” means that the result warrants further medical investigation or treatment because it may have impact on a person’s health status.

On the I visit, participants will then return to the study clinic 3 weeks after administration of the second study injection, V2+28 (+7) days. Interim medical histories and concomitant medications will again be reviewed with the participant and blood specimens will be collected for immunogenicity analyses.

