# Study Evaluations

## 8.1 Clinical Evaluations

Safety evaluations will be made by a clinician on visits V1, V1+7, V2, V2+7 and V2+28 through targeted physical exams. Evaluation must be performed before and after administration of study product on V1 (day 0) and V2 (day 28). Reported signs and symptoms will be recorded by the participant on Participant Diary from Days 1-7 and Days 28-35 in the study.

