## 9.6 Halting Rules

Study enrollment and dosing will be halted and an ad hoc DSMB review/recommendation will be performed if any of the following occur:

Study Halting Events:

1. One or more participant experiences ulceration, abscess, or necrosis at the site of injection associated with product administration.
2. One or more participant experiences laryngospasm, bronchospasm, or anaphylaxis within 24 hours following administration of study product that is associated with product administration.
3. One or more participant experiences a study injection related SAE (excluding laboratory related SAEs, which will be managed as described in section 9.3.8).

1. Two or more participants experience generalized urticaria within 72 hours that is associated with product administration.
2. During the 7 days after each study injection, any of the following occurs across all treatment groups:

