**For the first 100 subjects:**

- - Five or more participants who received at least one study injection to date experience severe (Grade 3/4) study injection-related local reaction of the same category other than measured erythema or induration.
  - Three or more participants who received at least one study injection to date experience a severe (Grade 3/4) study injection-related systemic reaction of the same category (excluding laboratory AEs, which will be monitored separately).
  - Three or more participants who received at least one study injection to date experience a severe (Grade 3) study injection-related abnormality in the same laboratory parameter.
  - Two or more participants who received at least one study injection to date experience a severe (Grade 4) study injection-related abnormality in the same laboratory parameter.

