**After the first 100 subjects enrolled:**

- - 8% or more participants who received at least one study injection to date experience severe (Grade 3/4) study injection-related local reaction of the same category other than measured erythema or induration.
  - 4% or more participants who received at least one study injection to date experience a severe (Grade 3/4) study injection-related systemic reaction of the same category (excluding laboratory AEs, which will be monitored separately).
  - 2% or more participants who received at least one study injection to date experience a severe (Grade 3/4) study injection-related abnormality in the same laboratory parameter.

These halting rules refer to adverse reactions suspected to be vaccine related.

Butantan retains the right to temporarily suspend or prematurely discontinue this study at any time related to safety. If the study is stopped or suspended prematurely, Butantan will inform the local principal investigator as well as regulatory authorities about the decision and the reasons for termination or suspension. If such action is taken, all efforts must be made to ensure the safety of the participants enrolled in the study. The principal investigator will assist Butantan in informing the responsible IRB/ethics committee and provide the reason for the suspension or termination. In case of premature study or study clinic closure, the monitor will conduct all activities as indicated in the Clinical Monitoring Plan.

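### The laboratory halting criteria count only the 7 days after each injection, but the S1 and S2 safety bloods are due on days 7 to 10, and the protocol does not say whether results from days 8 to 10 count

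*Protocol*

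**What the plan says.** Section 9.6 lists events that halt enrollment and dosing pending an ad hoc DSMB review. The last of them opens with "During the 7 days after each study injection, any of the following occurs across all treatment groups", and all the laboratory criteria sit beneath it:

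- First 100 subjects: three or more participants who "experience a severe (Grade 3) study injection-related abnormality in the same laboratory parameter".
- First 100 subjects: two or more participants who "experience a severe (Grade 4) study injection-related abnormality in the same laboratory parameter".
- After the first 100: "2% or more participants who received at least one study injection to date experience a severe (Grade 3/4) study injection-related abnormality", again in the same parameter.

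The bloods that would supply these results are described in section 4 (Study Design). After the first injection: "Participants will return to the study site seven days after study injection, visit S1 on V1+7 (+3) days". After the second: "participants will return to the study site seven days after the second study injection, V2+7 (+3) days". Table 1 gives the same timing. The tolerance runs forward only.

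The protocol disagrees with itself on whether there is a further post-injection safety panel. Section 8.2.1 and the table in 8.2.3 schedule hematology and biochemistry at V2 as well. The hematology and biochemistry rows of Table 1, the V2 visit description in 7.2.5 and the safety analysis in 11.5 list no such draw.

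**The concern.** A halting rule should count the data collected to feed it. Here the counting window closes on the day the sampling window opens. A related Grade 3 or 4 result from a blood drawn on schedule on day 8, 9 or 10 is, on a literal reading, not counted. Whether a result counts would then depend on which day the appointment fell, and sites or the DSMB could treat identical results differently.

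No other halting criterion catches these results. The criterion on injection-related SAEs excludes laboratory SAEs and refers them to section 9.3.8, which contains no halting provision. The systemic-reaction criteria also exclude laboratory events, on the ground that these are monitored separately. The laboratory criteria are therefore the only stated automatic laboratory stop, in the first clinical evaluation of IB160 (section 1.1) and the first human use of both antigen-adjuvant combinations (section 1.6.1).

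The consequence reaches section 11.6. Enrollment may continue during the first DSMB review if no halting rule has been met, and that review need not be complete before second injections unless one has. An uncounted result leaves both running.

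**Working it through.** **Step 1. The calendar.** Section 8.1 labels the day of V1 as day 0, so the 7 days after an injection end on day 7. S1 and S2 are due at +7 (+3) days, so the permitted draw days are 7, 8, 9 and 10.

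- Inside the window: day 7, which is 1 of 4 days.
- Outside the window: days 8, 9 and 10, which is 3 of 4 days.

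**Step 2. The V2 panel.** V2 is due at V1+28 (+7), days 28 to 35 after the first injection, with blood taken before the second. If the panel exists, it adds 8 permitted days, all outside. Inside is then 1 of 12 permitted post-injection-1 draw days, and outside is 3 + 8 = 11 of 12. The V2 blood volume in Table 1, 39.5 mL, equals 30.5 + 4 + 5 mL (influenza serology, hematology, biochemistry in 8.2.3), which fits a safety draw at V2 even though the Table 1 rows do not mark one.

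**Step 3. Is a plan figure available to reproduce?** The protocol gives no operating characteristics for the halting rules. Its one binomial calculation, Table 8, does reproduce: 1 − (1 − 0.05)^54 = 93.7% (stated 94%) and 1 − (1 − 0.01)^162 = 80.4% (stated 80%).

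**Step 4. Illustration of the effect on the rule.** Let p be the true probability of a related abnormality of the relevant grade in one parameter, and f the share of panels drawn on day 7. If only day-7 panels count, the number counted in the first 100 is X ~ Bin(100, p·f). Neither p nor f is in the protocol, and both are assumptions. The calculation also assumes one panel per participant, independence between participants, and an abnormality rate that does not depend on the draw day.

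Worked case, p = 0.05 and f = 1: P(X ≥ 3) = 1 − [0.95^100 + 100·0.05·0.95^99 + 4950·0.05²·0.95^98] = 1 − (0.0059 + 0.0312 + 0.0812) = 0.88.

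Probability that the three-or-more Grade 3 criterion fires in the first 100:

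| Assumed p | f = 1 (all count) | f = 0.75 | f = 0.50 | f = 0.25 |
| --- | --- | --- | --- | --- |
| 2% | 0.32 | 0.19 | 0.08 | 0.01 |
| 3% | 0.58 | 0.39 | 0.19 | 0.04 |
| 5% | 0.88 | 0.73 | 0.46 | 0.13 |
| 8% | 0.99 | 0.94 | 0.77 | 0.32 |

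The column f = 0.25 corresponds to draws spread evenly over days 7 to 10. At p = 5%, the two-or-more Grade 4 criterion gives 0.96, 0.89, 0.72 and 0.36 across the same columns.

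S1 and S2 both feed the rule, so counting one panel per participant simplifies it. The comparison across columns matters more than any single value.

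**The case against.** A reader might infer three stronger things, and the protocol supports none of them.

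First, that S1 and S2 are the only scheduled post-injection safety bloods. Sections 8.2.1 and 8.2.3 say otherwise. A V2 panel would not close the gap, since it lies outside the window too, but its existence is an open contradiction and not a settled fact.

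Second, that a blood drawn on day 8, 9 or 10 can never trigger a halt. Section 9.6 asks when the abnormality occurs, and the protocol does not say that a laboratory abnormality is dated by its draw. Section 7.2.3 heads S1 as the seventh-day visit, and section 11.5 describes the safety bloods as those of days 7 and 35. A DSMB could reasonably treat any S1 or S2 panel as the 7-day result. Against that, sections 9.3.1 and 9.3.6 apply the 7-day limit strictly to solicited events, and for a silent laboratory change the draw date is normally the first date on which it can be seen. On any reading, a draw on day 7 counts, and so does an earlier unscheduled draw under section 7.5.

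Third, that the rule misses most of its data. That follows only if draws are spread across the tolerance days. Day 7 is the target and days 8 to 10 are tolerance, so a share of 75% or more on day 7 is plausible, and the loss is then modest.

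There are also safeguards. Section 11.6 has the DSMB review S1 safety data for the first 100 participants by visit, with no 7-day cut. Section 7.2.3 requires review of S1 results within 36 hours of receipt. Sections 7.6.2 and 9.6 allow suspension at any time. A severe late-window result would therefore be seen. What stands is that these routes rest on judgement, or on a review that does not by itself pause dosing, and do not replace the automatic halt.

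**Conclusion.** The point holds as an internal inconsistency in a participant-safety rule. The laboratory criteria are confined to 7 days after injection, and the panels that feed them are due on days 7 to 10. Read by draw date, results from three of the four permitted days fall outside, and the text does not say whether they count. The sections that disagree about a V2 safety panel add a second ambiguity of the same kind.

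The calendar mismatch rests on the protocol alone. The probabilities do not: they depend on an assumed event rate and an assumed share of day-7 draws, and they show only that the rule's sensitivity could range from nearly unaffected to largely lost. Because this is the only automatic laboratory stop and the correction is small, it should be made.

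**What to change.** Reconcile section 9.6 with the S1 and S2 sampling window in section 4 and Table 1. Separately, reconcile sections 8.2.1 and 8.2.3 with the Table 1 rows, 7.2.5 and 11.5 on whether a V2 safety panel exists. After both, the protocol should state unambiguously which scheduled and unscheduled laboratory results count towards the laboratory halting criteria, and by which date an abnormality is assigned to the window. Which passage changes is for the sponsor and the DSMB to decide.

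The cost is a short clarification in 9.6, the matching wording in the DSMB charter, and a consistency edit on V2. Aligning the windows needs no new threshold, visit or sample.

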**For the first 100 subjects:**

- - Five or more participants who received at least one study injection to date experience severe (Grade 3/4) study injection-related local reaction of the same category other than measured erythema or induration.
  - Three or more participants who received at least one study injection to date experience a severe (Grade 3/4) study injection-related systemic reaction of the same category (excluding laboratory AEs, which will be monitored separately).
  - Three or more participants who received at least one study injection to date experience a severe (Grade 3) study injection-related abnormality in the same laboratory parameter.
  - Two or more participants who received at least one study injection to date experience a severe (Grade 4) study injection-related abnormality in the same laboratory parameter.

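### For the first 100 subjects, two Grade 3 results plus one Grade 4 in the same laboratory parameter trigger no automatic halt, although three Grade 3 results do

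*Protocol*

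**What the plan says.** Section 9.6 of the protocol makes the consequence of a halting event mandatory: "Study enrollment and dosing will be halted and an ad hoc DSMB review/recommendation will be performed if any of the following occur". One group of events is counted over a short window and over all arms together: "During the 7 days after each study injection, any of the following occurs across all treatment groups".

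Within that group, the list headed "For the first 100 subjects" has two laboratory limbs:
- three or more injected participants "experience a severe (Grade 3) study injection-related abnormality in the same laboratory parameter";
- two or more injected participants "experience a severe (Grade 4) study injection-related abnormality in the same laboratory parameter".

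The systemic limb in the same list uses the same count of three but pools the grades: "Three or more participants who received at least one study injection to date experience a severe (Grade 3/4) study injection-related systemic reaction". It leaves laboratory events out. The local limb pools the grades as well. After the first 100 are enrolled there is a single laboratory limb, at 2% or more of those injected to date, and it is pooled too: participants who "experience a severe (Grade 3/4) study injection-related abnormality in the same laboratory parameter".

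The limb for a related SAE halts on one case, but with an exception: "excluding laboratory related SAEs, which will be managed as described in section 9.3.8". Section 9.3.8 says when an out-of-range value is an AE or an SAE. It contains no halting threshold.

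**The concern.** A halting rule should not become less sensitive when one of the cases is worse. Here it does. If one of three Grade 3 results in a parameter is replaced by a Grade 4, the count in the first limb drops to two, the count in the second is only one, and the automatic halt disappears.

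The stricter limit of two for Grade 4 is a reasonable choice and is not in question. The fault is only that a Grade 4 result does not also count towards the limit of three.

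At stake is the early phase of a study that gives these antigen-adjuvant combinations to humans for the first time (section 1.6.1). Meeting a halting rule is what makes the stop and the ad hoc DSMB review compulsory. Under section 11.6 it also decides whether enrollment may run on during the DSMB review of the first 100, and whether second injections must wait for that review.

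**Working it through.** **The plan's own figures.** The protocol states no operating characteristic for the halting rule. Its only power figures are in Table 8, for seeing at least one event. They reproduce (1 − 0.95^54 = 93.7%, stated 94%; 1 − 0.99^162 = 80.4%, stated 80%) but do not bear on this point.

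**Step 1: which patterns escape.** Let a be the number of participants at Grade 3 and b the number at Grade 4, all related and in the same parameter. As written, the rule halts if a ≥ 3 or b ≥ 2. With a pooled first limb it halts if a + b ≥ 3 or b ≥ 2.

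| (a, b) | As written | Pooled |
|---|---|---|
| (3, 0) | halt | halt |
| (2, 1) | no halt | halt |
| (1, 1) | no halt | no halt |
| (0, 2) | halt | halt |
| (1, 2) | halt | halt |

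The written rule does not halt when a ≤ 2 and b ≤ 1. The only such point with a + b ≥ 3 is (2, 1), so the two rules differ there and nowhere else.

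**Step 2: how long the gap lasts.** One more related Grade 3 or Grade 4 result in that parameter ends it, giving (3, 1) or (2, 2). Otherwise it ends when the pooled limb starts: 3/101 = 2.97% exceeds 2%. Three cases still reach the limit at 150 injected (3/150 = 2.00%) but not at 151 (1.99%). So a (2, 1) pattern standing at the switch halts at once.

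**Step 3: lead time, upper end.** Assume that enrolled equals injected, that results are immediate, and that exactly three of the first 100 are affected. The position of the third case is the maximum of three draws from 1 to 100, with mean 3 × 101/4 = 75.75. The mean lead of the fix over the 101st injection is 101 − 75.75 = 25.25 participants (range 1 to 98). The lead is at least 51 with probability C(50,3)/C(100,3) = 19,600/161,700 = 12.1%. Second injections due in that window would be additional; the protocol gives no enrollment pace.

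Two features of the protocol shorten the lead. Safety samples are drawn 7 to 10 days after injection (Table 1), so some of the first 100 will be read under the pooled limb. And the switch is tied to enrollment, which section 11.3 defines by consent, with screening up to 30 days before the first injection (section 7.1). On that definition the pooled limb could apply with, say, 80 injected, where 3/80 = 3.75% halts immediately.

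**Step 4: chance of the pattern.** The protocol gives no laboratory event rates, so these are assumptions. For one parameter and 100 participants, P(2,1) = 485,100 × p3² × p4 × (1 − p3 − p4)^97, where 485,100 = 100!/(2! 1! 97!).

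| Grade 3 rate | Grade 4 rate | P(2,1) |
|---|---|---|
| 0.2% | 0.05% | 0.08% |
| 0.5% | 0.1% | 0.7% |
| 1% | 0.2% | 3.0% |
| 2% | 0.5% | 8.3% |

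The lower end is more plausible, because screening values of Grade 2 or above are exclusionary (section 5.3) and most Grade 4 limits in Table 5 are extreme. One exception makes mixed grades easier to picture: bilirubin with any ALT/AST increase is Grade 3 at 1.51–1.75 × ULN and Grade 4 above that.

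**Step 5: whole-trial effect.** Simulation of 432 participants with immediate results (60,000 runs per scenario) gave the same trial-wide laboratory halt probability with and without the fix: 0.8%, 7.6%, 36.1% and 90.7% for the four rate pairs. Once enrollment passes 100, the fix changes when the halt comes, not whether it comes.

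**The case against.** **The bullet may mean Grade 3 or higher.** Both laboratory bullets call the event severe, and a Grade 4 value has passed the Grade 3 threshold, so nested limits may have been intended. The text does not say so. Adjacent bullets write Grade 3/4 when both are meant, and Grade 4 has its own bullet. The worst-severity sentence in section 9.3.2 does not settle it, because it concerns the analysis and not the halting count. If the nested reading was intended, the edit only states it.

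**Other safeguards are not merely discretionary.** This stands. A reader might infer that nothing but judgement covers the case, and the protocol does not support that. First safety-visit results must be reviewed within 36 hours of receipt (section 7.2.3). Grade 2 and above at either safety visit must be assessed for significance and relatedness and repeated (section 8.2.1). The DSMB must formally review the first 100 (section 11.6). None of these forces a halt of enrollment and dosing, however. The DSMB review needs first safety-visit data and so comes late in the window, and second injections need not wait for it unless a halting rule is met. Suspension by the sponsor (sections 7.6.2 and 9.6) is a matter of judgement.

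**The SAE limb may catch it.** This stands in part. The exclusion points to section 9.3.8, which concerns test values. A Grade 4 participant with a related clinical SAE, such as a hospitalization, could arguably halt the study alone. The certain gap is a Grade 4 value without one.

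**The consequence is slight.** This also stands, and it sets the severity.

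**Conclusion.** The point holds as a minor one. On the text of section 9.6, two related Grade 3 results plus one related Grade 4 in the same parameter do not trigger the automatic halt for the first 100 subjects, while three Grade 3 results do. Nothing in the protocol explains that ordering, and its other pooled limbs point the other way.

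The size is one count pair in one parameter, over a limited period. Under the assumed rates the chance is 0.08% to 8.3% per parameter, more plausibly near the lower end. Those figures might be read as halts that the trial would never make. They are not: if enrollment passes 100, the pooled limb halts every such case. The gain is an earlier mandatory stop, and the 25-participant mean lead is an upper-end value resting on enrolled equal to injected and on immediate results. That two of three or more affected participants could in general go unnoticed, or that the Grade 4 limit of two is itself wrong, does not follow either.

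**What to change.** In section 9.6, in the three-participant laboratory bullet for the first 100 subjects, replace Grade 3 by Grade 3/4. Keep the two-participant Grade 4 bullet and all counts as they are. Only the outcome at two Grade 3 plus one Grade 4 changes.

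The cost is one term in the protocol and the matching trigger check. No new data are needed. The downside is a slightly higher chance of an early temporary halt.
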